## ELIGIBILITY CRITERIA

4

Patient inclusion criteria are as follows: (1) men or women aged >18 years; (2) patients who require a change of bladder catheter; (3) absence of symptoms compatible with infection; (4) indication of bladder catheterization for 4 weeks; (5) maintained cognitive and physical capacity for self‐monitoring of the catheter valve; and (6) signed consent agreement.

Patient exclusion criteria are as follows: (1) symptoms of current UTI; (2) use of current antibiotic treatment or in the 2 weeks prior to inclusion in the study; (3) patients with malformations in the urinary tract; (4) immunocompromised patients; (5) patients with urological cancer; (6) patients who require continuous urine drainage (in the case of patients in the study arm) or hourly urine output measurement; (7) catheter insertion requiring more than one attempt; and (8) inability to read and understand Spanish.

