##### Magnitude of infections

The magnitude of infection will be obtained from the analysis of urine culture samples taken from patients twice, during inclusion (time 0) and during withdrawal of the catheter (time 4 weeks; Table 1). In the event that the patient is prescribed an antibiotic for a UTI before the 28th day, the magnitude of infection will be evaluated at the time of prescription, through the analysis of a urine culture sample, according to usual clinical practice. The research staff will take between 5 and 10 mL of urine sample in a sterile container which will be transported to the laboratory in the shortest time possible (<2 h). If the transport or processing cannot be performed immediately, the sample will be refrigerated between 2°C and 8°C without exceeding 24 h until processing. The second urine sample will be collected from the new catheter inserted at the follow‐up visit. After seeding the urine in specific culture media, the microorganisms that have grown in the culture will be analysed to determine the number and type of microorganisms present using techniques based on biochemical tests and Matrix‐Assisted Laser Desorption/Ionization Time‐Of‐Flight (MALDI‐TOF) type mass spectrometry.

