##### Rate of symptomatic and asymptomatic infections

The magnitude of infection obtained from the urine samples will be classified according to the following criteria based on the European Association of Urology (EAU) clinical guidelines^29^:
Symptomatic infection: The presence of pathogenic microorganisms in amounts greater or equal to 1000 Colony Forming Units/mL (CFU/mL) accompanied with symptoms will determine the existence of the infection.Asymptomatic infection: In the absence of infection symptoms, a quantity of microorganisms greater than or equal to 100 000 CFU/mL will indicate asymptomatic infection.

In addition to the presence or absence of infections to assess their rate, this variable will also be collected using the outcome measure “infection‐free days” (with a maximum possible value of 28 days) to be compared between Foley‐type catheters and T‐Control. Suppose the patient at some point prior to the follow‐up visit presents symptoms compatible with UTI. In that case, a urine culture will be performed to confirm the presence or absence of urinary infection, according to usual clinical practice. In the event that the patient receives an antibiotic for a UTI while he/she takes part in the study prior to the follow‐up visit, this will be recorded in the medical record. However, the patient will also be asked about it at the follow‐up visit when he hands in his/her incident diary, and this will be counted as an infection.

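### Asymptomatic infection is defined without reference to the time-0 culture, and a UTI antibiotic counts as an infection without regard to the culture result

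*Protocol article*

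**What the plan says.** All references are to the protocol article.

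- **Objective (section 3).** A secondary aim is to compare infections, symptomatic and asymptomatic, that are due to the catheter.
- **Definitions (section 5.4.2, rate of infections).** Symptomatic: at least 1000 CFU/mL of pathogens plus symptoms. Asymptomatic: at least 100 000 CFU/mL without symptoms. Neither mentions the earlier culture.
- **Cultures (section 5.4.2).** Samples are "taken from patients twice, during inclusion (time 0) and during withdrawal of the catheter". If symptoms arise earlier, "a urine culture will be performed to confirm the presence or absence of urinary infection, according to usual clinical practice". If an antibiotic is prescribed for a UTI before day 28, "the magnitude of infection will be evaluated at the time of prescription, through the analysis of a urine culture sample".
- **Antibiotic rule (same section).** "In the event that the patient receives an antibiotic for a UTI while he/she takes part in the study prior to the follow‐up visit", it is recorded. The patient is also asked about it on returning the diary at follow-up, and "this will be counted as an infection".
- **Infection-free days (same section).** The infection variable is also expressed in days, "with a maximum possible value of 28 days".
- **Entry (section 4).** Participants need a change of an existing catheter. Screening on infection is by "absence of symptoms compatible with infection" and by no antibiotic use currently or in the previous 2 weeks. Bacteriuria is not an exclusion.
- **Blinding (section 2.4).** Patients, health professionals, research team and monitors are unblinded; laboratories and data analysis are blinded.
- **Table 1 (section 5.4).** The microbiology laboratory is the source for rate of infection, at baseline and 4 weeks. Catheter-related antibiotics are a separate row, sourced from patients and professionals.

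**The concern.** Two features of the definitions pull the infection outcome away from its stated target.

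First, a patient above 100 000 CFU/mL at entry and again at 4 weeks meets the asymptomatic definition at the second sample, although the bacteria were there before the study catheter. In people already catheterised long term this could be common. It would mask a real device effect, and at about 25 per arm a chance difference in baseline status could look like one.

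Second, the culture taken on symptoms is meant to settle whether infection is present, but the antibiotic rule does not wait for its result. A treated patient with a negative culture is still counted. The decision to prescribe is made by people who know the arm, so part of case finding moves from the blinded source named in Table 1 to an unblinded one. The Discussion lists infections among the items measured with objective and subjective tools, a strength it sets against the lack of blinding. It also ranks UTI magnitude and ratio among the most important data to collect.

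**Working it through.** **1. The plan's own figures.** The protocol gives no infection rate and no sample size for infection. Its only design figure is 25 per group for quality of life. With d = 0.95, two-sided 2.5% and 80% power (sidedness and power are assumed, being unstated), the noncentral-t calculation gives 23 per group, and 23/0.95 = 24.2, so 25. That figure reproduces and does not depend on this point. With 5% dropout, 25 × 0.95 = 23.75, about 24 evaluable per arm.

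**2. Carry-over of baseline bacteriuria.** Let b be the share positive at entry, assumed to stay positive in both arms, and p the incidence among the rest.

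Observed rate = b + (1 − b)p, so the observed difference = (1 − b)(p_Foley − p_T-Control).

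Assume p = 40% versus 20%, 24 per arm, two-sided 5%. Power by normal approximation with pooled variance under the null:

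| b | Foley | T-Control | Difference | Power | n per arm for 80% |
|---|---|---|---|---|---|
| 0% | 40% | 20% | 20 points | 32% | 82 |
| 20% | 52% | 36% | 16 points | 20% | 150 |
| 40% | 64% | 52% | 12 points | 13% | 265 |
| 60% | 76% | 68% | 8 points | 9% | 494 |
| 80% | 88% | 84% | 4 points | 6% | 1181 |

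The 5% level is an assumption. The analysis plan prints 0.005 beside 95% intervals; at 0.005 every power would be lower. Power is already low at b = 0, as is to be expected in a pilot; the relevant column is the difference.

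**3. Chance imbalance.** With 25 per arm and independent binomial counts of baseline positives, an imbalance of 5 or more patients (20 points) has probability 11% at b = 20% or 80%, and 19% at b = 40% or 60%. With equal incidence p in both arms, a 20-point imbalance separates the observed rates by 20 × (1 − p) points: 16 points at p = 20%, 12 at p = 40%, with no device effect.

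**4. Antibiotic rule.** Let r be the true infection rate and f the share of uninfected patients given a UTI antibiotic. Counted rate = r + (1 − r)f. Assume r = 20% in both arms:

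| f Foley | f T-Control | Counted Foley | Counted T-Control | False difference |
|---|---|---|---|---|
| 10% | 10% | 28% | 28% | 0 points |
| 20% | 10% | 36% | 28% | 8 points |
| 30% | 10% | 44% | 28% | 16 points |
| 10% | 30% | 28% | 44% | −16 points |

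Equal prescribing creates no false difference; unequal prescribing can push either way. One extra counted course moves an arm's rate by 1/24 = 4.2 points.

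**5. Infection-free days.** Symptom onset and antibiotic start have dates. Asymptomatic onset does not: scheduled cultures fall only at time 0 and 4 weeks, so onset between them is unobserved, and a patient positive at entry has no clear starting value.

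**The case against.** The strongest reply on the baseline culture is that the definitions only classify a sample. Table 1 lists the infection rate at both time points, and an analysis plan not shown here could adjust for baseline. That is fair as to adjustment. It does not change the case definition printed here, under which unchanged bacteriuria at 4 weeks is an infection.

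A reader might infer that carry-over contaminates every infection outcome and biases the comparison. The document does not support that. Symptoms and recent antibiotics bar entry, so a later symptomatic episode is new in onset, and carry-over chiefly affects the asymptomatic category. Randomisation balances entry status in expectation, leaving dilution and chance imbalance. The dilution factor also assumes that no baseline positive clears and that the device does nothing in those patients.

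On antibiotics, the rule has a sound purpose: treatment can suppress the 4-week culture, so a treated patient might otherwise be classed as uninfected. Early cultures follow usual practice, and an episode known only from the diary may have none. A reader might conclude that every unconfirmed course should be dropped; that would create the opposite error. This part of the objection stands and shapes the fix. UTI antibiotics are also a separate secondary outcome, so the prescribing component can be seen. The counting sentence nevertheless carries no condition on the culture.

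On infection-free days, the derivation and choice of method may properly sit in the analysis plan.

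**Conclusion.** Both defects hold, in secondary endpoints that the protocol itself labels preliminary.

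1. The asymptomatic definition counts persistent pre-existing bacteriuria as infection on the study catheter. The difference in that category is diluted by about (1 − b) if baseline positives persist, and small arms add chance imbalance. The prevalence b is not given, so the size is illustrative over b = 20% to 80%.
2. The antibiotic rule lets unblinded prescribing into the infection rate. This is the only one of the two that can bias systematically, and in either direction. The 8- and 16-point examples rest on assumed prescribing gaps; the document gives no evidence that prescribing will differ by arm.

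Infection-free days are sound for datable symptomatic events but not for asymptomatic onset. Nothing here touches the primary endpoints or the 25 per group. The wording should be changed before data lock, because the infection comparison is the trial's preliminary effectiveness measure.

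**What to change.** - **Asymptomatic infection.** Count it as new only if the time-0 culture was below 100 000 CFU/mL or a new species appears at 4 weeks, and/or adjust the 4-week comparison for time-0 culture status. Adjustment keeps every patient in the comparison.
- **Symptomatic infection.** Make symptoms plus at least 1000 CFU/mL the main definition, using the cultures already planned at symptoms or prescription.
- **Treated episodes.** Report courses with a negative culture under the antibiotic endpoint. Keep treated episodes with no culture as a separate unconfirmed category, not as uninfected. Give the present antibiotic-inclusive count as a sensitivity analysis.
- **Infection-free days.** Base them on datable symptomatic events; leave the time-to-event method to the analysis plan.

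**Cost.** Wording only, with no extra samples and no change to care; species identification is already planned. The price is fewer counted events and some episodes left unconfirmed. Confirmation is also an imperfect filter: symptoms are still reported unblinded, and a patient already carrying more than 1000 CFU/mL will meet the culture part of the definition whenever symptoms are reported.

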##### Indication of antibiotic treatments associated with catheter use

At the end of the follow‐up visit, antibiotic treatments will be recorded along with the dose and treatment time.

##### Determination of the biofilm formed in the catheters and identification of the microorganisms present

The catheter removed will be sent to the laboratory, and with the help of sterile gloves and scissors, a 1 cm‐sized fragment corresponding to the part below the balloon will be cultured for each catheter to assess whether biofilm is present or absent. The microorganisms forming the biofilm will be quantified as CFU per catheter piece. These microorganisms will also be identified by means of MALDI‐TOF‐type mass spectrometry to establish statistical relationships with those identified in the urine cultures. In the event that during the course of the 14 days in which the patient will be catheterized, he receives antibiotic treatment due to a UTI, this will be taken into account when analysing the results obtained in the catheter's biofilm determination.

##### Number of adverse events related to catheterization

The type and number of adverse events will be registered in the Patient's Clinical Data Notebook: accidental disconnection of the catheter, obstruction, pain, loss of urine per catheter, haematuria, and accidental spills caused by the professional during insertion. The patient will receive a Patient Incident Diary to write down the incidents, along with other information that may be of interest during catheterization. Timing and source of adverse events data are summarized in Table 1.

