T‐Control is a new silicone Foley catheter with an integrated valve to voluntarily control urine flow, which enables bladder filling and its conscious regulation and emptiness, thereby reducing mucosa irritation by contact of the catheter tip. This innovative valve controls urine flow by means of three different positions, from the proximal end of the tube. The “open” and “closed” positions regulate urine flow without other additional accessories required by the conventional Foley catheter. The third or “insertion” position, only available initially for the insertion manoeuvre, prevents unwanted urine leakage thanks to a specific built‐in membrane. T‐Control has an additional safety lock to prevent accidental opening of the catheter valve.

T‐Control has undergone and passed different biocompatibility studies, including the assessment of cytotoxicity, skin sensitization, intracutaneous reactivity (irritation), and acute, subacute, and subchronic systemic toxicity (necessary results to obtain the Conformité Europeéne marking). Beyond these preclinical biocompatibility studies, usability studies have also been performed to test the ease of professional handling of T‐Control. These confirm that an easier and safer insertion technique could be provided, while also being able to be performed by one person, which reduces the staffing needs currently recommended by clinical practice guidelines.^24^ Furthermore, patients' experience in the use of bladder catheters were comparatively evaluated with T‐Control and conventional catheters and recognized the added value and the intuitive and ease of use of T‐Control.^25^ Finally, in vitro studies have observed how T‐Control significantly prevented/delayed the formation and growth of biofilm during the first 5 days, compared with conventional Foley‐type catheter.^26^ In addition, another pilot clinical study is currently being carried out with the T‐Control catheter in patients with acute urinary retention (NCT05643950), for which the first results are expected to be obtained at the end of the first quarter of 2024.

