## ENDPOINTS

3

The general purpose of this study is to determine the effectiveness, comfort, and experience of the patient catheterized with T‐Control® compared with patients with a conventional Foley catheter, by evaluating patients with long‐term urinary catheters.

Primary endpoints are as follows:
To analyse, through qualitative techniques, the comfort and acceptability of the T‐Control® device for the patient framed in the course of the disease, identifying preferences and training and information needs for the use of the device; andTo analyse and compare the degree of satisfaction and levels of self‐perceived health‐related quality of life of patients with both types of catheters.

Secondary endpoints are as follows:
To assess the preliminary effectiveness of T‐Control versus a common Foley catheter, by comparing the magnitude and rate of infections (both symptomatic and asymptomatic) due to the catheter among long‐term catheterized patients. Additionally, evaluate the effectiveness of T‐Control by comparing the days free of infection on the 28th day after catheterization;To compare the indication of antibiotic treatments associated with catheter use between the conventional Foley‐type catheter and the T‐Control device;To determine the biofilm formed in the catheters and identify the microorganisms that form this to evaluate its relationship with the onset of symptomatic and asymptomatic infections as well as different adverse events;To compare the number and relevance of adverse events related to bladder catheterization between T‐Control and the traditional Foley catheter;To assess the preliminary cost‐effectiveness of T‐Control versus the traditional Foley catheter from the public healthcare services perspective; andTo measure and compare the level of satisfaction and workload perceived of health professionals with both types of catheterization by means of a questionnaire at the end of the study.

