#### Intervention arm: T‐Control catheter

5.1.1

The T‐control catheter is a flexible, silicone tube with an inflatable balloon at the distal tip, a polytetrafluoroethylene (PTFE) membrane integrated into its body, and a sliding fluid control valve. The valve, built into the catheter, provides additional functions to the catheter, such as turning urine flow on and off after insertion (functions currently provided by accessories such as caps or valves) and controlling urination during the insertion process (function not provided by any other device). Accidental loss of urine can thus be avoided from the first moment of use until its withdrawal. In addition, it has a safety cap that reduces the possibility of accidental valve movements before use or during transport and fixing. The design has been developed in such a way that, once inserted, it facilitates autonomous use even for the elderly or patients with limited manual dexterity. The device is sterile and single‐use, like any conventional Foley catheter.

The continuous use of a single device of T‐Control cannot exceed 30 days. The cumulative use for each type of T‐Control device can exceed 30 days.

T‐Control is manufactured, sterilized, and packaged by the subcontracted company Conod Medical Co., Ltd under the specifications of Rethink Medical and under its quality standards, as well as its accessory holder, also manufactured and packaged by the same subcontracted company.

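### The named adverse-event list counts staff spills at insertion, which T-Control is built to prevent, but names no valve-specific harm, so a total over the list may lean toward T-Control

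*Protocol article*

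**What the plan says.** The secondary endpoint in section 3 is "To compare the number and relevance of adverse events related to bladder catheterization between T‐Control and the traditional Foley catheter". Section 5.4.2 (number of adverse events related to catheterization) says that type and number go into the Patient's Clinical Data Notebook and then gives the types: "accidental disconnection of the catheter, obstruction, pain, loss of urine per catheter, haematuria, and accidental spills caused by the professional during insertion". The list is not introduced as a set of examples and has no entry for other events.

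On the device, section 1 says that the insertion position "prevents unwanted urine leakage thanks to a specific built‐in membrane". Section 5.1.1 describes "controlling urination during the insertion process (function not provided by any other device" and adds: "Accidental loss of urine can thus be avoided from the first moment of use until its withdrawal". The Discussion treats spillage as an occupational risk for health personnel.

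On collection, Table 1 has two rows. Events during insertion are observed by the health professional at baseline. Events during the catheterization period come from the participant or carer through the diary and notebook at 4 weeks. Section 5.2 allows any incident to be written in the diary. Section 2.4 says that patients, health professionals, the research team and monitors are not blinded.

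**The concern.** An adverse-event comparison is fair when the categories cover the foreseeable faults of both devices and are sought in the same way in both arms. Here one category, spills by the professional, belongs to the process of insertion and to staff exposure more than to patient harm. The article presents its prevention as a function unique to T-Control. The foreseeable faults of the new component, a sliding valve that the patient opens and closes, have no category of their own.

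If the six types are added up, the conventional catheter can collect events that T-Control is designed not to produce, while T-Control's own faults enter the count only if a patient thinks to write them down and someone then assigns them to a heading. Two things are at stake: the direction of a raw between-arm count, and how well the device's own risks are captured in what the Discussion calls its second clinical trial.

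**Working it through.** The article gives no expected adverse-event rate, so there is no planned figure to reproduce. The check is mainly a comparison of the text.

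**Step 1. Each named type against the device description.**
- *Spills by the professional at insertion:* a declared design target (sections 1 and 5.1.1), described as a function that no other device offers, and classed as an occupational matter in the Discussion.
- *Loss of urine per catheter:* also a declared target (section 5.1.1), but it works both ways, because a leaking or accidentally opened T-Control valve would be recorded here. Section 1 acknowledges accidental opening by describing a lock against it.
- *Obstruction, pain, haematuria:* ordinary catheter harms that can occur in either arm.
- *Accidental disconnection:* the text says disconnection of the catheter. Nothing ties it to a T-Control design claim.

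**Step 2. What the article recognises about the valve, against the list.** Section 1 describes open and closed positions. Inclusion criterion 5 in section 4 requires cognitive and physical capacity to manage the valve. Exclusion criterion 6 bars study-arm patients who need continuous drainage. The article thus treats operation of the valve as critical, yet no named type covers valve malfunction, inability to operate it, or retention with it closed. The usability check by professionals in section 5.4.2 concerns packaging and instructions, not failure in use.

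**Step 3. How each kind of event is found.** A spill is a named item, observed by staff at the moment it happens. A valve fault during the 4 weeks depends on an unprompted diary entry by a patient who knows the allocation. The article does not say whether diary incidents outside the six types are coded and counted.

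**Step 4. Can these items matter to a raw count?** The only figure taken from the article is 25 patients per group (section 5.3). All rates below are assumptions, chosen to show direction only.
- Spills in a proportion f of Foley insertions and none with T-Control add 25 × f events to the Foley count: f = 0.10, 0.30, 0.50 gives 2.5, 7.5, 12.5.
- Valve or retention events in a proportion v of T-Control patients and none in controls add 25 × v events if all are counted: v = 0.04, 0.10, 0.20, 0.30 gives 1, 2.5, 5, 7.5.
- The net contribution (T-Control minus Foley) is 25 × (v − f). It runs from 25 × (0.04 − 0.50) = −11.5 to 25 × (0.30 − 0.10) = +5.

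So the treatment of these two items can change the sign of their contribution to a raw total. This does not estimate the bias. A valve event recorded as pain or obstruction is already in the count, and controls fitted with a cap or valve could have similar events.

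**The case against.** The strongest reply is that nothing is actually omitted. The diary takes any incident and is a source for events during catheterization. The follow-up questionnaire asks about complications with the catheter and accessories. Emergency visits and admissions come from the clinical record, and monitoring covers safety issues. The notebook (Data S3) and diary (Data S4) are not shown and may contain further categories. Table 1 already collects insertion events apart from later ones, and no section prescribes a single unweighted total, since the endpoint concerns number and relevance. Finally, this is one of several secondary endpoints in a 50-patient pilot.

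Much of this stands. A reader might infer that valve harms are excluded from the safety data; the open diary shows that they are not. A reader might also take disconnection to mean disconnection of accessories that T-Control does not need; the text does not say so, and the point does not use it. Nor is the whole list slanted, because three of the six types are general harms and urine loss can count against T-Control.

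What the reply does not remove is the stated list itself. It places staff spills among the adverse events and names no fault of the new valve. Table 1 separates the two kinds of event at collection but does not say that they stay separate in the comparison. An open diary is a weaker means of finding events than a named item observed by staff.

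**Conclusion.** The point holds in a limited form. The named list includes a staff and usability outcome that, on the article's own account, only T-Control is built to prevent, and it has no valve-specific category. Events of the second kind can still be reported, but unprompted and unblinded. A total over the named types may therefore lean toward T-Control.

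This rests on two assumptions: that spills enter the total being compared, and that naming an item raises the chance that it is recorded. The size cannot be derived from the article. A reader might go further and state a definite number of spurious events, or call the safety comparison demonstrably biased. With no event rates given and the forms not shown, the documents support neither. The change is still worth making because the lean is foreseeable and cheap to remove.

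**What to change.** In section 5.4.2 and the matching notebook and diary forms:

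- (a) Add three event types, asked in identical terms in both arms: valve or cap malfunction or inability to operate it; retention with the valve or cap closed; and leakage around the catheter. Including caps keeps the question fair to controls, since section 5.1.1 notes that flow control is currently provided by such accessories.
- (b) Report spills by the professional at insertion as a separate procedural outcome, outside the patient adverse-event total.
- (c) State that diary incidents outside the named types are coded and counted.

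If the unseen forms already contain such items, the change reduces to aligning section 5.4.2 with them. The cost is a few extra form items and some wording. The drawback for the sponsor is that the T-Control event count may look less favourable.
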